## **II. Research Plan and Design**

**A. Study Objectives:** The broad research goal of this study is to provide novel data regarding the potential efficacy of multimodal exercise to reduce frailty in pwMS and will set the foundation for our long-term goal of identifying novel interventions to improve the quality of life of persons with MS. The specific aims of the project will be to determine the feasibility of a multimodal exercise training in pwMS (Aim 1), and to explore the effects of the multimodal exercise training on frailty in pwMS (Aim 2).

**B. Study Type and Design:** Using a pilot single-blind randomized controlled trial (RCT) study design, ambulatory individuals living with MS will be allocated to 6 weeks of multimodal exercise training (n=30) or to a waitlist control group (n=30) (Figure 1).

[figure not shown]

Figure 1. Study design.

The following outcomes will be collected to accomplish the study aims:

**Aim 1: Feasibility Outcomes:** The following outcomes, based on the guiding principles for feasibility studies, will be utilized to examine the feasibility of the Virtual Reality and Resistance Training for MS (VRRT4MS) program in the study population: a) participant recruitment, i.e., number of consented individuals/number of approached individuals (expressed as a percentage); b) retention rate, i.e., number of participants completing the intervention/number of participants enrolled at baseline (expressed as percentage); c) appropriateness of data collection and training procedures, as quantified through the percentage of missing data for analysis purposes (i.e., missing items in the frailty index) and through time spent in training, respectively; d) participant safety, i.e., number of adverse and serious adverse outcomes throughout the study and self-reported pain, assessed by the numeric pain rating scale, during each training session (the Borg and Omni scales of perceived exertion will also be administered throughout each training session to differentiate exertion from pain); e) evaluation of resources, i.e., difference between proposed and actual research timeline; f) user engagement, i.e., study participant feedback questionnaire. We note that the effects of VRRT4MS on the primary frailty outcome, namely the frailty index (AIM 2), will also represent a further feasibility outcome of the intervention.

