### **C. Sample size, statistical methods, and power calculation**

1. Descriptive statistics (frequency/percent and mean/SD) will be mainly used to summarize participants' characteristics and intervention outcomes. The means and 95% CIs for pre-post changes in the primary (i.e., frailty index) outcome will be estimated. No imputation will be considered for missing data. The Wilcoxon rank sum test will be used for comparing the pre-post changes in frailty index between the two groups. The intervention will be considered feasible if the retention rate and the proportion of completed sessions are more than 80%. Pre-generated randomization codes will be prepared by the biostatistician ([name]). The randomization ratio will be 1:1.
2. [name], who will be the assessor for the study assessments, will be blinded to which group the participants have been allocated to. Participants will be aware of which group they are in. The study coordinator and [name] will have access to the code to the blind. The code will not need to be broken unless there are unforeseen circumstances in which [name] needs to know which group a particular participant was assigned to. Following the baseline assessment (visit 2), participants will be randomized to one of the two groups based on pre-generated randomization codes prepared by the biostatistician, [name]. In accordance with the CONSORT guidelines, sequence generation, allocation concealment and group allocation will be blinded and separate processes.
3. For this pilot study, we plan to enroll a convenience sample of 60 ambulatory people (30 per group) with Multiple Sclerosis living with frailty that meet inclusion/exclusion criteria. These subjects will provide feasibility data and preliminary efficacy data for designing a future study if the findings are promising. We expect a 15% dropout rate, and at that at least 24 subjects per group will complete the study.

**D. Subject Criteria (See Vulnerable Populations appendix, if applicable):** We will enroll 60 ambulatory pwMS living with frailty. During Visit 1, we will screen subjects for frailty based on established cut-offs according to the Fried phenotype. This screening tool was chosen to ensure a time- and cost-effective identification of pwMS who are frail.

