Once participants meet the screening criteria, they will attend the first study assessment (Visit 2 – baseline assessment). During this visit, participants will undergo the blood draws in the morning, in fasting conditions (i.e., at least 12 hours of fasting), at the Landon Center on Aging (laboratory tests listed in Table 1 – see biomarkers). After the blood draw, participants will complete a comprehensive battery of physical and cognitive tests, self-reports, clinical measurements, and nutritional status measures (see Table 1) in the Human Performance Laboratory at the Landon Center on Aging. These procedures will take about 90 minutes. At the end of the visit, they will be provided with a wearable sensor consistent with our previous work. From these assessments, we will derive 70 health-deficit items that will be used to calculate a frailty index according to the guiding principles of the deficit accumulation model. A synopsis of the frailty index is provided in Table 1. The health-deficit items will be coded on a 0-1 scale, to indicate the absence or presence of health deficits, using standard validated procedures by a single researcher experienced in frailty assessments and blinded to group allocation (PI [name]). The frailty index score will be calculated as the

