| Function in ADLs               | 6             | MSQoL-54                                          | Questions about the ability to perform ADLs                                                                                                                                   |
| Energy                         | 5             | MSQoL-54, MFIS                                    | Questions about tiredness, energy, and fatigue                                                                                                                                |
| Psychosocial function          | 6             | MSQoL-54, MFIS                                    | Questions about participation in social activities, feelings of happiness, downheartedness, etc                                                                               |
| Health attitudes/sleep quality | 6             | Wearable sensor (worn for three consecutive days) | Number of daily steps, number of 30-seconds walking bouts, moderate to vigorous physical activity, total physical activity, number of hours spent sleeping, sleep efficiency. |
| Cognition                      | 6             | CVLT-II, SDMT, BVMT, TMT, MFIS                    | Total words recalled, Total BVMT score, Raw SDMT score, TMT times, self-reported memory problems.                                                                             |
| Physical performance           | 6             | Instrumented gait analysis, 6MWT, Dynamometry     | Self-selected gait speed, functional ambulation profile, 6MWT distance, handgrip strength, knee extensor strength, 5X chair stand.                                            |
| Nutritional status             | 5             | Laboratory tests, Self-report.                    | BMI, serum albumin, appetite disorders, problems with cooking.                                                                                                                |
| Comorbidities                  | 16            | Medical records, Automated BP monitor, MSQoL-54.  | Polypharmacy, systolic BP, diastolic BP, comorbidities; fall history                                                                                                          |

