| Biomarkers                     | 12            | Laboratory tests                                  | NfL, BDNF, GFAP, CRP, IL-6, IL-10, TNF-alpha, IFN-gamma, and CXCL9, mi-RNAs.                                                                                                  |

**Legend:** ADL: activities of daily living, MSQoL-54: 54-item multiple sclerosis quality of life questionnaire, MFIS: modified fatigue impact scale, CVLT-II: California verbal

learning test, SDMT: symbol digit modalities test, BVMT: brief visuospatial memory test; TMT: trail making test, 6MWT: 6-minute walk test, BP: blood pressure, BMI: body mass index, CRP: c-reactive protein.

All study outcomes will be assessed in a standardized manner during Visit 2 and 3. Following visit 2, participants will be randomized to one of the two groups based on pre-generated randomization codes prepared by the biostatistician. In accordance with the CONSORT guidelines, sequence generation, allocation concealment and group allocation will be blinded and separate processes. Participants will then either complete the waitlist period (passive control) or attend the exercise training visits 3 times a week, for 6 weeks, totaling 18 training visits. Each training visit will last one hour. The training visits will take place at the Laboratory for Advanced Rehabilitation Research in Simulation at the University of Kansas Medical Center.

**Intervention (Multimodal exercise) Group:** Participants will complete 15 minutes of virtual reality treadmill training (VRTT), followed by 30 minutes of progressive evidence-based resistance training (RT), followed by other 15 minutes of VRTT. This interval training design was chosen to induce acute fatigue before the last bout of VRTT. See Table 2.

**Table 2.** The Multimodal exercise program.

| Exercise components      | Duration   | Description                                                                                                                    | Target (frailty domains)*             |
|--------------------------|------------|--------------------------------------------------------------------------------------------------------------------------------|---------------------------------------|
| 1) VR treadmill training | 15 minutes | Treadmill walking with interactive virtual environment.                                                                        | - Slowness
- Cognition             |

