| 2) RT                    | 30 minutes | Seated leg press, seated hamstring curls, seated calf raises, seated chest press, seated lat-pulldowns, seated shoulder press. | - Muscle weakness
- Shrinkage      |
| 3) VR treadmill training | 15 minutes | Treadmill walking with interactive virtual environment.                                                                        | - Slowness, Cognition
- Exhaustion |

**Legend:** VR: virtual reality, RT: resistance training, \* The multimodal exercise program will also inherently target the 'inactivity' component of frailty.

Both the VR and RT components of the program will be individualized based on the participant's abilities and the training progression will be adjusted every 2 weeks. Over-ground gait speed will be assessed prior to the intervention and every two weeks thereafter and will be utilized to set the treadmill speed for the VR component. As part of VR, participants will navigate through a virtual environment projected on a TV screen while receiving feedback from the system (Figure 2). The RT component will consist of performing evidence-based RT exercises, as fully described in Table 2. In the event participants are unable to complete 15 minutes of continuous walking, walking duration will be progressively increased in 1–3-minute bouts until the prescribed time is reached. The estimated 1-repetition maximum (1-RM) of all RT exercises will be evaluated using validated standard procedures (for untrained individuals) prior to the intervention. At the beginning of the intervention, participants will complete 3 sets of 8-12 repetitions at 20-30% of the 1RM and slowly progress up to 80% over the course of 8 weeks. The end point of each set will always be limited to volitional fatigue. Recovery periods of 2-4 minutes will be prescribed between sets and exercises.

**Control Group:** Participants randomized to the control group will be put on a waitlist (passive control group) for 6 weeks. Upon completion of Visit 3, participants in the control group will be able to receive the intervention, if they wish so.

[figure not shown]

Panel A

[figure not shown]

Panel B

Figure 2. Gait Better (TM) virtual reality (VR) treadmill training set up. Panel A. Camera detects markers on feet and projects them on screen. Panel B. View of VR monitor depicting individual's virtual feet, visual distractors, and obstacles.

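### At least 19 of the 70 frailty-index items are rated by participants who know their group, so the pooled change and the effect size passed to the later RCT may be inflated

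*Protocol*

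**What the plan says.** Section II.B describes the design: "Using a pilot single-blind randomized controlled trial (RCT) study design". Section II.C.2 says whom the blinding covers. The named assessor, "who will be the assessor for the study assessments, will be blinded to which group the participants have been allocated to", is masked, and the same section states "Participants will be aware of which group they are in". Section II.E.2 adds that the index items are coded "by a single researcher experienced in frailty assessments and blinded to group allocation".

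The arms differ in contact. Exercise participants "attend the exercise training visits 3 times a week, for 6 weeks, totaling 18 training visits", each lasting one hour. For the comparator, "Participants randomized to the control group will be put on a waitlist (passive control group) for 6 weeks", with the intervention offered after Visit 3.

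The primary frailty outcome (II.B, Aim 2) is one index of 70 items, each coded from 0 to 1, summed and divided by the number of possible deficits (II.E.2, Table 1). Some items are questionnaire answers about feelings and daily life. The psychosocial row, for example, is described as "Questions about participation in social activities, feelings of happiness, downheartedness, etc". Sections I.A (Aim 2) and II.B treat a change above 0.03 as clinically meaningful. Sections I.A (Aim 1), I.B.1 and II.C.3 say that the results will inform a later, fully powered trial.

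**The concern.** Masking the assessor or coder protects an item only if that person makes the judgement. In a questionnaire item the participant makes it, and the coder only transcribes it. Participants here know whether they have trained three times a week or have been waiting. Questions on energy, mood, social participation and perceived health are plausibly sensitive to that knowledge and to the attention that comes with supervised sessions.

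The planned analysis (II.C.1 and V.A) works on the pooled 70-item change. In that single number, a change in how participants rate themselves is mixed with a change in measured function. At stake is the estimate that the pilot hands on. If part of it reflects expectation and attention, the later RCT would be planned on too large an effect, and V.B's expected reduction in frailty would be read too confidently.

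**Working it through.** **Inputs.** Item counts and sources: Table 1. Index formula and 0-1 coding: II.E.2. Threshold 0.03: I.A (Aim 2) and II.B. Recommended minimum of 30 items: I.B.3.

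**1. Reproduce the index length.** 2 + 6 + 5 + 6 + 6 + 6 + 6 + 5 + 16 + 12 = 70, as the protocol states.

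**2. Count the items that come only from questionnaires.** Domains whose only sources are MSQoL-54 and/or MFIS: global health 2 + ADLs 6 + energy 5 + psychosocial 6 = 19. Share of the index: 19/70 = 27%.

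This is a floor. Self-reported memory problems sit in cognition, and appetite and cooking problems in nutrition. Fall history sits in comorbidities and may be self-reported. Table 1 does not give the split. At one item each (an assumption) the total is 19 + 4 = 23, and 23/70 = 33%.

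**3. Put the threshold into items.** 0.03 × 70 = 2.1 deficit points. For one participant with absent/present coding, two items give 2/70 = 0.029 (below) and three give 3/70 = 0.043 (above).

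**4. Group level.** Index shift = (mean shift per self-rated item × 19)/70, with the other 51 items unchanged.

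| Mean shift per item | Shift in the index |
|---|---|
| 0.05 | 0.05 × 19/70 = 0.014 |
| 0.08 | 0.08 × 19/70 = 0.022 |
| 0.11 | 0.11 × 19/70 = 0.030 |

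The exact break-even is 2.1/19 = 0.111 per item, or 2.1/23 = 0.091 with 23 items. For the exercise arm's own pre-post change, the shift is that arm's. For the comparison of arms, it is the difference in shift between them.

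**5. Planning consequence, as an illustration.** Suppose the observed difference were 0.030 and a 0.05 shift per item supplied 0.014 of it. The remainder is 0.016. At the same SD, the required sample size scales with the inverse square of the difference: (0.030/0.016)² ≈ 3.5. A shift too small to reach 0.03 alone could therefore still matter for planning. Both starting values are hypothetical.

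**6. Is a companion index feasible?** 70 − 19 = 51 items. Removing four further self-reported items leaves 47, and removing five leaves 46. All exceed 30.

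**The case against.** Several stronger readings are tempting, and the protocol does not support them.

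- *The trial is mislabelled.* A reader might set the single-blind label against the unblinded participants. There is no contradiction: the assessor is masked, and participants' awareness is disclosed. They cannot realistically be blinded to treadmill and resistance training.
- *Expectation alone will produce a meaningful result.* This is shown only as arithmetic. Reaching 0.03 needs an average shift of 0.11 over all 19 items, including ADL function. The three-item figure concerns one person, whereas the planned test compares group changes. The 0.03 expectation in I.A is attached to change in the exercise group.
- *The waitlist has no contact at all.* The text says only that it is passive.
- *The exposed share is well above 27% because comorbidities hardly move.* That domain contains blood pressure and fall history, so it cannot be treated as fixed.
- *The effects can never be separated.* Items are recorded by domain and source, so the split can be made from data already collected.

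It is also fair to say that Aim 2 is exploratory, that the feasibility criterion rests on retention and completed sessions, and that fatigue and mood may truly improve with exercise. An unseen SAP might already contain an analysis of the observed items, so its absence here is not counted as an error.

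What stands is narrower. The composition of the index, the passive comparator and the reach of the blinding are fixed in this protocol. Together they leave at least 27% of the primary frailty outcome without protection from participants' knowledge of their group.

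**Conclusion.** The point holds as a limit on what the blinding can protect and on what the pooled estimate can mean. At least 19 of 70 items (27%) are unblinded self-report against a passive control, so the 70-item change and the resulting effect size may be inflated.

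The size is unknown, because the protocol gives no figure for an expectation or attention effect. About 0.11 per item would match the threshold unaided, and smaller shifts would contribute in proportion. The count of 19 rests on Table 1 alone. The higher count of 23 and the lower end of the 46 to 51 range rest on assumed item splits.

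The consequence is mainly for planning the later RCT and for the wording of Aim 2 conclusions. The feasibility criterion on retention and sessions is not affected. This is a worthwhile, inexpensive improvement and not a fatal flaw.

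**What to change.** - **II.C.1 and V.A:** keep the 70-item index as the primary frailty outcome. Before unblinding, list the items that the participant does not rate and define a companion index from them (about 46 to 51 items). Analyse it exactly as the full index (mean change with 95% CI, Wilcoxon rank sum test). Report it and the self-report sub-score beside the full index.
- **V.B:** state that the full-index effect includes unblinded self-report against a passive control, and that both estimates will be considered when the later RCT is planned.

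A rule that frailty reduction may be claimed only if the companion index moves in the same direction is not advised. With no effect it would be met about half the time by chance.

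The cost is a few sentences and one repeated analysis, with no new data, visits or participants. The companion index will be shorter and somewhat noisier, and it omits domains in which exercise may give real benefit, so it should sit beside the full index and not replace it. It is better protected but not immune, because performance tests depend on effort and sensor items on behaviour. Fixing the item list before unblinding matters, since a split chosen afterwards could look selective.

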**K. Personnel who will conduct the study, including:**

1. Indicate, by title, who will be present during study procedure(s): PI, Co-I, study coordinator, research technician, and GRAs.
2. Primary responsibility for the following activities, for example:
  - a. Determining eligibility: [name], study coordinator with assistance from PI ([name]).
  - b. Obtaining informed consent: PI ([name]) and [name]
  - c. Providing on-going information to the study sponsor and the IRB: PI ([name]), study coordinator
  - d. Maintaining participant's research records: study team
  - e. Completing physical examination: GRAs
  - f. Taking vital signs, height, weight: GRAs
  - g. Drawing / collecting laboratory specimens: Landon Center on Aging
  - h. Performing / conducting tests, procedures, interventions, questionnaires: [name] and GRAs.
  - i. Completing study data forms: study team
  - j. Managing study database: study coordinator and PI ([name])

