When research personnel learn that a participant has experienced an adverse event, research personnel will contact the PI on the same day to receive instructions for the transfer of the participant for treatment and follow-up of the adverse event. In addition, research personnel will complete an adverse event form. Participants with adverse events are eligible to remain in the trial unless there is withdrawal of consent. Participants who have experienced a serious adverse event will be withdrawn from the study.

The investigator will communicate with the participant and primary care physician (if deemed necessary by PI) to acquire information to complete the treatment questions on the adverse event form. The specific questions are: no action taken (i.e., further observation only); intervention temporarily interrupted; intervention permanently discontinued due to this adverse event; patient hospitalized. The investigator will continue to communicate with the participant and primary care physician until resolution to record change of severity, change of suspected attribution to intervention, and change of treatments for the adverse event.

The investigators and the Data and Safety Monitoring Board will review Adverse Events and Serious Adverse Events. If unexpected experimental-related adverse events emerge during the course of the trial, then the investigator will report the adverse events to the Institutional Review Board and the National Institutes of Health within the timelines required by each entity.

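### The PI is named as the blinded sole coder of the frailty index, yet holds safety and data duties that reveal the arm of some participants; custody of unassigned allocation codes also needs stating

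*Protocol*

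**What the plan says.** Section II.B describes the trial with the words "Using a pilot single-blind randomized controlled trial (RCT) study design". Section II.C adds that participants know their group and that the assessor does not, so the blind rests on those who measure and code the outcome.

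**Coding.** Section II.E says that the frailty-index items are coded "by a single researcher experienced in frailty assessments and blinded to group allocation (PI [name" (the name is removed from the public copy).

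**Safety and data.** Section II.L says that after an adverse event "research personnel will contact the PI on the same day to receive instructions for the transfer of the participant". It also has the PI review all adverse and serious adverse events as they arise. Section II.K makes the coordinator and the PI managers of the study database, and section IV.A gives the PI the highest level of data access.

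**Allocation.** Section II.C says "Pre-generated randomization codes will be prepared by the biostatistician" and promises that generating the sequence, concealing it and allocating participants are separate, blinded processes. It also says "The study coordinator and [name] will have access to the code to the blind". Section II.K has the line "Determining eligibility: [name], study coordinator with assistance from PI ([name".

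**Testing and training.** Section II.K has one line for both: "Performing / conducting tests, procedures, interventions, questionnaires: [name] and GRAs".

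**The concern.** The two arms differ completely in contact between Visit 2 and Visit 3. Exercise participants attend 18 training visits, and controls wait for 6 weeks with none (section II.E). An event reported from a training session, a note that training was interrupted or stopped, or a session record of pain, exertion or time in training can therefore belong only to the exercise arm. The protocol expects some of this: section II.F regards temporary muscle soreness as likely in that arm and stops a session when pain exceeds 3 on the rating scale.

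The PI receives or can open this information and is also the coder described as blinded. Both statements cannot hold for the participants affected. The primary frailty outcome passes through this one coder, and Aim 1 intends the effect sizes to inform a fully powered trial, so a biased estimate would be carried forward. Analysis cannot undo knowledge of the arm at the time of coding.

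The custody of the allocation code raises a second, conditional problem. If the code that the coordinator can see covers assignments not yet made, a person who determines eligibility could know the next assignment.

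**Working it through.** **1. Item count.** The domain counts in Table 1 are 2 + 6 + 5 + 6 + 6 + 6 + 6 + 5 + 16 + 12 = 70. This matches the 70 items stated in section II.E.

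**2. The PI's duties side by side.**

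| Duty | Section | Reveals the arm? |
|---|---|---|
| Sole coder, blinded | II.E | Must not |
| Same-day contact about an adverse event | II.L | Yes, if the event is tied to a session |
| Ongoing review of all events | II.L | Yes, where the form records that the intervention was interrupted or stopped |
| Database management, highest data access | II.K, IV.A | Yes, if training records are opened |

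The protocol describes no masked route to the PI and no restriction on these records. The safety board receives unblinded data quarterly, but this does not replace the PI's same-day role.

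**3. How many participants might be exposed through events.** The protocol gives no event rate, so the chance p of a reportable event per training visit is an assumption. With 18 visits attended, independent visits, and every report revealing the arm, the chance of at least one report is 1 − (1 − p)^18.

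| Assumed p | Chance of at least one report | Expected number of 30 |
|---|---|---|
| 0.5% | 8.6% | 2.6 |
| 1% | 16.5% | 5.0 |
| 2% | 30.5% | 9.1 |
| 5% | 60.3% | 18.1 |

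**4. What that could do to the arm mean.** The protocol's clinically meaningful change is 0.03, and 0.03 × 70 = 2.1 items. Suppose, purely for illustration, that the coder leaned by three items in the same direction for every exposed participant: 3/70 = 0.043 each. The shift in the exercise-arm mean is the exposed share times 0.043:

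- p = 0.5%: 0.086 × 0.043 = 0.004
- p = 1%: 0.165 × 0.043 = 0.007
- p = 2%: 0.305 × 0.043 = 0.013
- p = 5%: 0.603 × 0.043 = 0.026

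To reach 0.03, the exposed share would have to be 0.03 / 0.043 = 0.70, or 21 of 30. All four cases fall short of it.

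**5. What the code covers.** Section II.C calls the pre-generated list codes, and sets no limit of time or scope on access to the code to the blind. On that reading the coordinator could see future assignments. The next sentence, however, speaks of not needing to break the code except in unforeseen circumstances, which suits a key for participants already assigned. The text allows both readings. Only the first conflicts with the promised separation.

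**The case against.** Several stronger conclusions are tempting, and the protocol does not support them.

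- **That allocation is foreseeable at entry.** This needs the first reading in step 5. Section II.C also places randomization after Visit 2, and section III.B shares screening among several people: history and EDSS are checked before approach, and the PI and another person give the Mini-Cog and Fried tests. What stands is that the access is not limited in writing.
- **That the blind is lost altogether.** Event reports reveal the arm only of those who have one. Participants with a serious event are withdrawn (section II.L), so that route should seldom reach Visit 3 coding. Database access could widen the exposure, but nothing shows that the PI would open training records before coding.
- **That the PI judges relatedness to the intervention.** Section II.L gives that score to the investigators collectively.
- **That the testers are unblinded.** Section II.C says that the assessor is blinded. The personnel line in section II.K pools duties but does not show one person both training and testing the same participant. Names are removed, and section II.L mentions delegation lists in which duties could be separated.
- **That bias would exceed the clinical threshold.** The three-item lean is an assumption, and step 4 shows that it would need about 70% of the arm exposed. Many items are laboratory, sensor, blood-pressure or scored questionnaire values with little room for judgement.

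It is also fair to say that this is a pilot with a convenience sample, that its feasibility criteria (retention and completed sessions) do not depend on the coder's blinding, and that participants' own knowledge of their group affects self-reports in any case. These points limit the consequences. They do not reconcile section II.E with section II.L.

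**Conclusion.** The conflict over coder blinding stands on the text and does not depend on removed names, because section II.E identifies the coder by role as the PI. As written, the blinding cannot be kept for exercise participants with a session-linked event, or for anyone whose training records the PI sees before coding.

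The number affected is unknown: about 3 to 18 of 30 under assumed event rates of 0.5% to 5% per visit. The size of any bias is also unknown. The shifts of 0.004 to 0.026 in step 4 show scale under an invented lean and are not a forecast.

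The concealment point is conditional: access to the code contradicts the promised separation only if it extends to unassigned participants. The pooling of tests and interventions is a gap in wording, not a demonstrated failure.

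Together these should be fixed before Visit 3 coding begins, and code custody before further participants are randomized. They do not invalidate the trial.

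**What to change.** 1. **Coding.** Leave adverse-event reporting and the PI's safety role as they are. Derive the 70 items by a script whose cut-offs are locked before any Visit 3 data are seen. Alternatively, have an existing team member with no access to adverse-event or training records code them. In either case, restrict the coder's access to those records until coding is locked, and amend section II.E to match.
2. **Code custody.** State in section II.C that unassigned codes stay with the biostatistician or in REDCap, which the study already uses, and that nobody who determines eligibility can see them. Say also whether the code to the blind covers only participants already assigned.
3. **Testing.** State in section II.K or the delegation list that staff who perform a participant's Visit 3 tests have not trained that participant.

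The cost is protocol and delegation wording, some scripting work and less flexible staffing. The sample size, the visits and the safety reporting line do not change.
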